**5.3 Study Setting**

The study will take place in the NICU of Shaare-Zedek Medical Center

**5.4 Preliminary study**

**In order to establish safety , we will enroll infants admitted to the NICU to three successive treatment groups , as follows: the first group will include term infants admitted to the NICU (gestational age ≥37+6 and >7 days old), the second group will include near-term infants (gestational age > 34+0 to 36+6 weeks and >7 days old) and the third group will include premature infants (gestational age >30+0 to 33+6 and >=10 days old). We intend to enroll up to 20 patients in each group, for a minimum of 200 patient days per group (see sample size estimation). All infants will be assigned for bathing three times a week with washcloths impregnated with 2% chlorhexidine gluconate (Clinell ® Chlorhexidine wash cloths, GAMA healthcare) for the duration of their NICU stay. The infant’s skin will be monitored continuously as described below (see ‘6.0 Safety and monitoring’ and appendix 2). In case of grade 3 or 4 reactions, the study interventions will be temporarily suspended, and the adverse event will be reported to the Helsinky committee and to the study steering committee. If no grade 3 or 4 reactions will be encountered after at least 200 patient days per group, enrollment to the subsequent group will be performed (e.g if no grade 3-4 reaction will be encountered for 200 patient days in group 1, we will start enrolling patients for group 2 etc.). If no grade 3-4 dermatitis is encountered in the preliminary study, we will initiate enrollment as described below (‘5.5 intervention’)**

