A recent multicenter study examined the use of chlorhexidine-impregnated washcloths among adult patients at nine intensive care and bone marrow transplantation units. The chlorhexidine group had 23% lower rate of MDRO acquisition and a 28% lower rate of BSI compared with the control group ^13^. A systematic review of 15 studies, 9 of which were randomized controlled trials, provided support for the usefulness of CHG in a variety of healthcare settings including intensive care units, internal and surgical hospital wards ^[[20]](#endnote-20)^ .

Studies that examined the use of CHG in neonates were conducted mainly in developing countries and evaluated single whole body cleansing of the newborn immediately after birth, with or without maternal vaginal cleansing. CHG concentrations varied between 0.25% and 1%, and its use was associated with a reduction in neonatal mortality in high-mortality settings, but did not show benefit in low neonatal mortality settings^[[21]](#endnote-21)^’^[[22]](#endnote-22)^’^[[23]](#endnote-23)^’^[[24]](#endnote-24)^’^[[25]](#endnote-25)^’^[[26]](#endnote-26)^ . A large multicenter study in 10 pediatric intensive care units (PICUs) in the USA found that the incidence of bacteremia was 36% lower among patients receiving daily CHG bathing (3.28 per 1,000 days, 95%CI 2.27–4.58)) compared with patients receiving standard bathing practices (4.93 per 1,000 days, 95%CI 3.91–6.15 ). There were no serious study related adverse events^[[27]](#endnote-27)^.

Despite the fact that CHG was not approved by the US Food and Drug Administration for use in infants <2 months of age, it was used in large well-designed clinical trials on tens of thousands of neonates without reported serious adverse events^[[28]](#endnote-28)^’^[[29]](#endnote-29)^. Moreover, a recent survey in US NICUs found that the majority were using CHG, mainly for central venous catheter (CVC) site preparation and CVC maintenance ^[[30]](#endnote-30)^.

A recent study examined the effect of 2%CHG bathing on prevention of central-line associated bloodstream infection (CLABSI) in the NICU. Eligible infants were those with CVC weighing >1000 grams or those weighing <1000 grams after day 28 of life. Using a quasi-experimental study design the authors compared the rate of infection among infants before and after the intervention and demonstrated a decrease from 6 to 1.92/1000 CVC-days. No adverse events were reported^[[31]](#endnote-31)^.

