**5.5 Intervention**

All infants in the NICU eligible for the study will be assigned for bathing three times a week with washcloths impregnated with 2% chlorhexidine gluconate (Clinell ® Chlorhexidine wash cloths, GAMA healthcare) during the initial 6-months study period (intervention), followed by standard bathing during the second 6-months period, then again intervention period for 6 months and standard bathing for 6-months. Total study period- 2 years.

**Inclusion criteria**: infants weighing ≥1500 grams and ≥10 days of age; parents’ informed consent

**Exclusion criteria:** infants weighing <1500 grams or <10 days of age**;** parents’ refusal to sign informed consent.

For standard bathing procedure see appendix 1.

Before the study initiation, as well as at the beginning of each study period, nurses will be instructed on the proper technique for bathing patients. Bathing will be performed according to product brochure, three times a week.

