**5.8 Trial oversight:**

The steering committee of the study will include, except for the PI, two other Infectious Disease physicians ([name] and [name]). There will be biweekly discussions of the progress

report, reporting of compliance with active surveillance, reporting of compliance with

bathing, and any adverse reactions or other problems.

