**6.0 Safety and monitoring.**

A study that evaluated the tolerability of 2% CHG for catheter insertion antisepsis among infants ≥1500 grams and ≥7 days old found no significant dermatitis reactions^[[34]](#endnote-34)^. Seven of 48 infants had measurable CHG levels in the blood. In a trial that evaluated a multifactorial approach to reduce the rates of CLABSI, Andersen et al. noted that 4 of 36 neonates <1000g developed contact dermatitis after a 2% CHG scrub. There were no episodes of contact dermatitis in 49 study participants who were ≥1000g^[[35]](#endnote-35)^. The alternative for antisepsis in neonates is povidone-iodine. However, iodine absorption that may compromise thyroid function is one reason to explore the use of CHG. Although CHG was reported to be absorbed through neonatal skin in several trials, no significant systemic side effects were reported^[[36]](#endnote-36)^’^[[37]](#endnote-37)^. Animal trials showed no significant toxicity from CHG^[[38]](#endnote-38)^. The US Food and Drug Administration (FDA) states on the drug facts box of 2% CHG cloth:” use with care in premature infants or infants under 2 months of age. These products may cause irritation or chemical burns”.

Each participant’s skin will be examined daily by nursing staff and twice a week by study personnel.

Skin reactions will be graded and recorded on a standard report form (appendix 2).

Grade 3 and 4 skin reactions will be reported as serious adverse events.

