**6.1 Human subject research considerations**

*6.1.1 Human subjects involvement and characteristics*

This is a crossover study. The control will be the current bathing procedures in our NICU. The “intervention” will be the use of 2% chlorhexidine gluconate cloth which is FDA

approved for adult patient perioperative skin preparation and for use to reduce bacteria that can

potentially cause skin infection. ^[[39]](#endnote-39)^. The FDA states on the drug facts box of 2% CHG cloth:” use with care in premature infants or infants under 2 months of age. These products may cause irritation or chemical burns”.

Monitoring of any unexpected adverse effects or serious adverse events related to study

procedures will be the responsibility of the principal investigator and will be reported

immediately to the steering committee as well as the IRB. (see appendix c for SAE report form)

For the purposes of this research protocol *unexpected adverse events* and *serious adverse*

*events* will be defined as follows:

*Unexpected adverse event:* Any adverse reaction or experience that is not listed in the

current labeling for the drug product or investigators brochure. Known adverse reactions

to chlorhexidene containing topical products include irritation, sensitization, and generalized

allergic reactions. Chlorhexidine should be kept out of the ears and eyes.

*Serious adverse drug event.* Any adverse reaction or experience occurring at any dose that

results in any of the following outcomes: Death, a life-threatening adverse reaction,

inpatient hospitalization or prolongation of existing hospitalization and a persistent or significant

disability/incapacity.

*6.1.2 Potential risks*

Potential recognized risks of bathing with chlorhexidine include local skin irritation, allergic reaction and irritation of mucous membranes

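### Infants born at 30+0 weeks or earlier can enter main-phase chlorhexidine bathing without the protocol's own 200-patient-day safety step, and the visible text carries no suspension rule beyond the preliminary study

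*Protocol*

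**What the plan says.** Section 5.4 of the protocol sets up a preliminary study to establish safety. Three groups are bathed in succession: term, near-term, and a last one in which "the third group will include premature infants (gestational age >30+0 to 33+6 and >=10 days old". The synopsis gives the same lowest band, 30 to 34 weeks. A group opens only after the one before it has completed at least 200 patient-days with no grade 3 or 4 reaction, and the main phase opens only if the preliminary study shows no grade 3 or 4 dermatitis. The same section gives the action rule: "In case of grade 3 or 4 reactions, the study interventions will be temporarily suspended".

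Section 5.5 defines main-phase eligibility as "infants weighing ≥1500 grams and ≥10 days of age", plus parental consent. The exclusion criteria mirror this. Neither list has a gestational-age limit. Appendix 1 (standard bathing) has rows for <26 and for 27-30 weeks, so the unit's bathing policy covers such infants.

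For safety in general, section 6.0 says that each participant's "skin will be examined daily by nursing staff and twice a week by study personnel", and that "Grade 3 and 4 skin reactions will be reported as serious adverse events". Section 6.1.1 requires reporting "immediately to the steering committee as well as the IRB". Section 5.8 adds: "There will be biweekly discussions of the progress". None of these says that bathing stops.

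**The concern.** The protocol chose gestational age as the axis for its stepwise safety clearance, then opened the main phase on weight and postnatal age alone. The two rules do not cover the same infants. Those born at 30+0 weeks or earlier who have reached 1500 g and 10 days are eligible, but no step was designed for them. Sections 6.0 and 6.1.1 both repeat the product label's caution about premature infants and those under two months, so this is a stratum for which the sponsor would want its own rule to apply.

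The second part concerns action. In the visible text the only instruction to interrupt bathing after a grade 3 or 4 reaction sits in the preliminary study. From 5.5 onward the text provides for examination, grading, discussion and reporting. At stake is the safety conduct of the trial, not its efficacy inference.

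**Working it through.** **Coverage of the two rules, set side by side**

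| Gestational age at birth | Step in 5.4 | Eligible under 5.5 at ≥1500 g and ≥10 days |
|---|---|---|
| Term group | ≥200 patient-days | yes |
| >34+0 to 36+6 | ≥200 patient-days | yes |
| >30+0 to 33+6 | ≥200 patient-days | yes |
| ≤30+0 | none | yes |

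Gestational age is not defined. I read it as age at birth, because 5.4 gives days of age separately and Appendix 1 gives age at onset of bathing separately. Under a postmenstrual reading the gap narrows.

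**The plan's own figures (section 5.9)**
- Preliminary study: 1.2 minor reactions per 1000 patient-days against ten times that, in 500 patient-days. Expected counts are 0.6 and 6.0. With an exact Poisson test at one-sided 0.05 (my assumption; the protocol states neither alpha nor power for this part), the critical count is 3, actual alpha 0.023 and power 0.94. The statement holds. In one 200-day group the expected counts are 0.24 and 2.4, the critical count is 2 and power is 0.69.
- Main phase: 2.5 against 1.25 per 1000 (midpoint of the stated 2-3, halved). n per group = (1.960 + 0.842)² × (0.0025 + 0.00125) / 0.00125² = 18,837, within 2% of the stated 18,548. No figure is in dispute.

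**Exposure of the uncleared stratum**
- Required preliminary patient-days from infants at ≤30+0 weeks: 0 of at least 600.
- Share at which their main-phase CHG exposure equals one step: 200 / 18,548 = 1.1%.
- Their real share is not given. At an assumed 5%: 18,548 × 0.05 = 927 patient-days. At an assumed 20%: 3,710.
- Baths in one step: 200 × 3/7 = about 86.

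**What a clean step shows**
- Upper one-sided 95% limit for zero events in 200 patient-days: 2.996 / 200 = 15.0 per 1000.
- Chance of seeing no event at an assumed true rate of 5 per 1000: exp(−0.005 × 200) = 37%; over 600 patient-days, exp(−0.005 × 600) = 5%.

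**Maturity at first bath**
- Youngest group 3 infant: 30+1 plus 10 days = 211 + 10 = 221 days = 31+4 postmenstrual.
- Born at 27+0 (189 days): reaches 221 days on day 32.
- Born at 30+0, bathed on day 10: 31+3, one day younger.
- Born at 29+0 and, by assumption, already at 1500 g on day 10: 203 + 10 = 213 days = 30+3, eight days younger.

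**Cited tolerability (section 6.0)**
- 0 of 49 infants at ≥1000 g: upper one-sided 95% limit 1 − 0.05^(1/49) = 5.9% per infant.
- 4 of 36 at <1000 g: 11.1% (exact 95% CI 3.1% to 26.1%). Section 5.5 excludes that weight.

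**Cost of a whole-study suspension rule in the main phase**
- Chance of at least one trigger in 18,548 CHG patient-days: at an assumed 0.1 per 1000, 1 − exp(−1.85) = 84%; at 0.05 per 1000, 1 − exp(−0.93) = 60%.

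**The case against.** The strongest defence is that weight and postnatal age form a legitimate safety limit which the protocol supports with evidence. Section 6.0 cites a study of 2% CHG at ≥1500 g and ≥7 days without notable dermatitis, and the reactions it reports elsewhere were at <1000 g. The Background cites a NICU bathing study: "Eligible infants were those with CVC weighing >1000 grams or those weighing <1000 grams after day 28 of life", with no adverse events reported. Most infants born before 30 weeks will be well past day 10 when they reach 1500 g. This stands, and it keeps the added risk modest. It does not close the gap. The ≥1500 g study concerned catheter-site antisepsis rather than repeated bathing, and the bathing study was quasi-experimental in infants with central lines. The sponsor cites both and still required a stepwise clearance. Nor is the maturity difference capped at one day: 5.5 has no lower gestational limit, so a heavy infant born before 30+0 could be bathed on day 10 at a younger postmenstrual age than anyone in group 3.

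Several stronger readings are tempting and should not be drawn.
- A reader might infer that no suspension rule exists for the main phase. The content of Appendix 2, to which 5.4 and 6.0 refer for skin monitoring and grading, is not shown, so this can be said only of the visible text.
- A reader might infer that main-phase reactions go unmanaged. They do not: checks, serious-event reporting and regular committee review continue.
- A reader might infer that moving from one water bath to three CHG baths a week is peculiar to the uncleared stratum. Appendix 1's once-weekly row is 27-30 weeks; read in completed weeks it includes infants of 30+1 to 30+6, who are in group 3, so that change can already occur in the preliminary study.
- A reader might infer that the 5.4 rule should simply run through the whole trial. With a trigger on any single event, suspension would be likely even at very low rates.

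**Conclusion.** The mismatch is real and internal to the protocol: its stepwise safety rule stops at >30+0 weeks and its main-phase eligibility does not. The uncleared exposure exceeds one full step if the stratum supplies more than 1.1% of the required CHG patient-days. That figure is a yardstick for exposure, not a risk threshold, and the 5% and 20% shares are illustrations. Nothing in the protocol shows a raised reaction rate in these infants at ≥1500 g.

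The conclusion assumes that gestational age means age at birth. The part about the main-phase action rule does not depend on that reading, but it is limited to the visible text. No effect estimate, power or alpha is touched. This is an inexpensive safety improvement worth making, not a defect that threatens the trial.

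**What to change.** Keep the 5.5 eligibility and make these changes.
1. State in 5.5 that the first 200 CHG patient-days of infants born at ≤30+0 weeks are reviewed by the steering committee at its existing meetings, and that CHG bathing in this stratum is suspended pending review if a grade 3 or 4 reaction occurs. Say that gestational age means age at birth.
2. For the rest of the main phase, state in 5.5 or 6.0 that CHG is stopped in the affected infant and that the event triggers prompt steering-committee review. Do not make suspension of the whole study automatic on a single event.
3. Keep affected infants in the period's patient-day and event counts, so that the analysed population stays the same in CHG and control periods.
4. Report this stratum's skin reactions separately.

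The cost is one extra safety look and one extra table row. No infant is dropped and there is no delay. If the stratum is suspended, some CHG exposure is lost and the contrast is somewhat diluted.

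The in-period review observes these infants while they are being bathed, so it is not a gate before exposure, and a clean 200 days would still miss a rate of 5 per 1000 in 37% of cases. If a true gate is wanted, a short fourth preliminary group would raise the minimum from 600 to 800 patient-days, with a delay whose length the protocol does not allow one to derive.

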**1. Study Synopsis**

| Protocol Title | Evaluation of the Effectiveness of Chlorhexidine Bathing in Reducing Nosocomial Infections in the Neonatal Intensive Care Unit |
| --- | --- |
| Protocol Number |  |
| Sponsor |  |
| Primary objective | To determine if daily bathing with chlorhexidine impregnated  washcloths will reduce the incidence of bloodstream infections within the neonatal intensive care unit (NICU) . |
| Study design | This is a prospective, controlled; crossover study of daily bathing with no-rinse, 2% CHG impregnated washcloths versus bathing with water/soap or water according to gestational age and weight (e.g. standard bathing). The trial will take place in the NICU.  **In the preliminary phase of the study we will establish the safety of chlorhexidine bathing using Clinell ® Chlorhexidine wash cloths on three groups of patients: term infants admitted to the NICU; late preterm infants (34-37 weeks); preterm infants 30-34 weeks of gestation. Interim analysis for adverse events will be performed after each group of patients.**  **In the subsequent phases of the study,** all infants admitted to the NICU and enrolled in the study will be bathed three times a week with Clinell ® Chlorhexidine wash cloths during the initial 6-months study period (intervention), followed by standard bathing during the second 6-months period, then again intervention period for 6 months and standard bathing for 6-months. Total study period- 2 years.  Data collection will include all bloodstream infections as well as surveillance cultures |
| Number of subjects | Approximately 800 patients in both arms  **Up to 60 patients (at least 200 patient days) in the preliminary study** |
| Study population | Infants **>=10** days ,weighing **>=1500** grams admitted to the NICU |
| Duration of participation | Duration of NICU stay OR for the duration of invasive hardware (e.g intravacular catheters, nasogastric tubes etc. ) |
| Treatment | Bathing three times a week with either:  a.2% chlorhexidine gluconate cloth  b. water/mild soap +water |
| Assessment of efficacy | The primary efficacy endpoint will be the reduction in bloodstream infections incidence during those study periods where the 2% Chlorhexidine Gluconate Cloth will be utilized.  Additional study endpoints include overall incidence of colonization with multi-drug resistant organisms (MDRO) and time to colonization |

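### The stop and go rules in section 5.4 turn on grade 3-4 (apparently skin) reactions, so a related serious non-skin event is reported but holds nothing

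*Protocol*

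**What the plan says.** Section 5.4 sets three rules for the preliminary phase.

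- **Suspension:** "In case of grade 3 or 4 reactions, the study interventions will be temporarily suspended". The event then goes to the Helsinki committee and the steering committee.
- **Next, less mature group:** "If no grade 3 or 4 reactions will be encountered after at least 200 patient days per group, enrollment to the subsequent group" proceeds.
- **Main phase:** "If no grade 3-4 dermatitis is encountered in the preliminary study, we will initiate enrollment as described below".

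On what is graded, section 5.4 says that the infant's "skin will be monitored continuously as described below", pointing to section 6.0 and appendix 2. Section 6.0 says: "Skin reactions will be graded and recorded on a standard report form (appendix 2". It then classes skin reactions of grade 3 and 4 as serious adverse events. The content of appendix 2 is not shown.

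Other parts of the protocol deal with harm more widely:

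- The synopsis, under study design, says: "Interim analysis for adverse events will be performed after each group of patients". Its safety row counts hypersensitivity reactions among the events monitored.
- Section 5.8 puts on the steering committee's biweekly agenda compliance with "bathing, and any adverse reactions or other problems".
- Section 6.1.1 defines a serious adverse drug event by outcome (death, threat to life, hospitalization or its prolongation, lasting disability). It has unexpected effects, and serious events related to study procedures, reported at once to the steering committee and the IRB. It names generalized allergic reactions among the known effects of the product.

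**The concern.** The preliminary phase exists to establish safety before less mature infants are exposed, and then before the unit-wide study begins. The two go rules are affirmative: if the stated condition is met, enrollment follows. A rule of that kind should name every event that ought to stop it.

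The protocol recognises harm beyond the skin. It lists generalized allergic reactions as known, and section 6.0 reports systemic uptake after catheter-site antisepsis in infants of at least 1500 g and at least 7 days old: "Seven of 48 infants had measurable CHG levels in the blood". In this trial the cloths are used three times a week for the whole NICU stay. Yet no related serious systemic or allergic event appears in the rules that decide whether to go on. At stake is whether such an event produces a hold by default, or only if someone chooses to impose one.

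**Working it through.** The point concerns the wording of a decision rule, so the main check is to set the sections side by side.

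**1. Are the grades skin grades?** The suspension rule and the next-group rule say only reactions. Section 5.4 speaks of monitoring the skin, section 6.0 applies grades 3 and 4 to skin reactions, and the main-phase rule says dermatitis. A skin reading is the natural one, but appendix 2 could show otherwise.

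**2. Follow one event through the protocol.** Suppose that an infant in group 1 has a life-threatening allergic reaction related to the cloth, without a grade 3-4 skin finding.

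| Provision | What it requires |
| --- | --- |
| 6.1.1 | The event is serious and related, so it is reported at once to the steering committee and the IRB. No hold is stated. |
| 5.8 | It is discussed at a biweekly meeting. No hold is stated. |
| Synopsis | It enters the adverse-event analysis after group 1. No criterion or consequence is stated. |
| 5.4, suspension | Not triggered. |
| 5.4, next group | Condition met once 200 patient days have accrued; group 2 opens. |
| 5.4, main phase | Condition met as far as this event goes. |

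**3. Is there a link in either direction?** Section 6.0 carries grade 3-4 skin reactions into the serious-event category. Nothing carries serious events under 6.1.1 back into the rules of 5.4.

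**4. Which decisions are affected?** With up to 20 infants per group:

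- opening group 2, after up to 20 infants;
- opening group 3, after up to 20 + 20 = 40;
- starting the main phase, after up to 40 + 20 = 60.

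The synopsis gives about 800 infants for both arms. Only those present in intervention periods would be bathed with the cloths.

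**5. Does the sizing of the preliminary phase cover this?** Section 5.9 sizes it on minor skin reactions: 1.2 per 1000 patient days, with 500 patient days said to detect a ten-fold rate.

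- Expected events at the reference rate: 500 × 1.2/1000 = 0.6.
- Expected events at ten times that rate: 500 × 12/1000 = 6.0.
- Flagging the product at three or more events (a cut-off assumed here, since the protocol gives none), exact Poisson probabilities give a one-sided error of 0.023 and power of 0.94.

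The statement is plausible, but it concerns minor skin reactions only and says nothing about serious non-skin events.

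**6. Systemic uptake.** 7/48 = 14.6% (exact 95% CI 6.1% to 27.8%). This shows absorption, not harm.

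**The case against.** The strongest reply is that section 5.4 should not be read apart from the rest of the protocol. The synopsis places an analysis of adverse events, not only of skin grades, after each group. In a sequential safety phase such an analysis has little purpose except to inform the next step. Related serious events go at once to bodies that can halt the study, and section 5.4 does not forbid holding for other reasons. It sets a threshold for the hazard that the protocol treats as principal, irritation and chemical burns. Appendix 2 may also grade more than the skin.

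Much of this stands, and it limits the point. A reader might infer that skin grades are the only safety check between groups. The synopsis, 5.8 and 6.1.1 show that they are not. A reader might also infer that a non-serious allergic reaction would come up only in the steering committee's discussions. The synopsis covers it too, through the analysis after each group and the inclusion of hypersensitivity among monitored events.

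What does not fall away is the missing link. The analysis has no stated consequence, 5.8 provides for discussion and 6.1.1 for reporting, while 5.4 tells the team to proceed. It is also fair to say that the remedy keeps a judgement on relatedness. But it changes the default after that judgement from proceeding to holding.

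**Conclusion.** The point holds as a gap in a stated rule, not as an absence of oversight. Read literally, section 5.4 neither suspends bathing nor holds the next group or the main phase for a related serious event that lacks grade 3-4 skin findings. All three rules and all three go decisions are affected.

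This rests on reading the grades as skin grades. If appendix 2 also grades systemic signs, the gap is smaller. The word dermatitis in the main-phase rule is probably loose wording for the same set of reactions, and nothing here depends on it.

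It is tempting to put a probability on a wrong escalation. The documents do not support one. They give no rate for related serious non-skin events, and sections 3 and 6.0 cite no serious or significant systemic effects, so such events should be rare. Even an assumed rate would give only the chance that an event occurs, not the chance that the interim analysis, the steering committee and the IRB all let escalation go ahead. Nor does the blood-level figure show harm. The change is a cheap improvement, held with medium confidence because the grading form is not shown.

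**What to change.** Amend the paragraph in section 5.4 so that all three rules use one trigger:

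- **Trigger:** a grade 3-4 skin reaction, or any serious adverse drug event under 6.1.1 judged possibly related to the cloth. This includes a serious generalized allergic reaction.
- **Consequence:** bathing is suspended, and the next group and the main phase stay closed, until the steering committee and the ethics committee have reviewed the event.
- **Further condition for each step:** the adverse-event analysis promised in the synopsis is complete before each next group and the main phase open. Non-serious allergic reactions are considered there, without an automatic hold.

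The cost is one amended paragraph. Related serious events are already reported immediately, so the trigger needs no new data collection. The downside is an occasional short hold, sometimes for an event later judged unrelated, and a brief pause at each step while the analysis is finished. The ethics committee's review time is not given, so the length of a hold cannot be stated. Requiring an event to be both serious and possibly related avoids holds for mild reactions and for stays prolonged by the infant's own illness.
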